### Data management

Potential participants will be informed that the personal information collected during the study is confidential and stored safely at the University of Tabriz. Data management will be following the Data Protection Act 2018.

All questionnaires, records, and participants’ data are coded and stored correctly in locked cabinets. Only study researchers will have access to files linking a person’s study number to their name. The questionnaire, laboratory data, and medical records will be entered into the Excel database. During the study, only the principal researcher will have access to the prepared Excel files. Finally, a clean data set without identification will be generated and delivered to the biostatistician for statistical analysis. All essential documents, including source documents, will be retained at least 5 years after completing the study.

The data monitoring team will assess data quality control at the beginning and end of the study. This team monitors the exact implementation of the study based on the approved protocol, and for this purpose, they compare the data in the database with the source documents to evaluate its accuracy and completeness.

### Statistical analysis

The collected data will be analyzed by the statistical package for the social sciences (SPSS) version 23 software. Descriptive statistics, including frequency, percentage, and central indices and dispersion, will be done. The Wilcoxon signed-rank test will determine the normal distribution of the data. If data distribution is normal, to compare the serum markers and physical components analysis among the study groups in the pre-intervention stage, independent sample *t*-test, and after the intervention, analysis of covariance (ANOVA) will be used by modulating the baseline values and probable variables. A paired-samples *t*-test will be used to compare data in each study group if the data distribution is normal, compared to the serum markers and physical components analysis before the study, Mann-Whitney test, and the study groups. In that case, Wilcoxon signed-rank test will be used (for both before and after the intervention). In all tests, the *p*-value < 0.05 will be considered significant. Missing data will be removed from the final analysis. The number of dialysis sessions per week and the participants’ blood sugar levels will be matched at the beginning of the study. Other confounding factors such as energy intake, BMI, gender, and age will be adjusted if needed.

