### Participants

In this study, the target population is patients with diabetes mellitus undergoing hemodialysis. The inclusion criteria are:

□ An age ≥ 20 years

□ Body mass index = 18.5–30 kg/m^2^

□ Having type 2 diabetes mellitus

□ Two or three times per week hemodialysis

□ Being on hemodialysis for at least 6 months

□ Ability and willingness to cooperate in the study

The exclusion criteria are:
Having inflammatory or infectious diseasesReceiving steroidal or nonsteroidal anti-inflammatory drugsSmokingUsing NS oil regularlyChanges in treatment methods (dialysis)

The hemodialysis process for all patients will be through capillary dialysis filters of polysulfone and bicarbonate dialysis solution. In case of changes in hemodialysis method or type of dialysis filters, the person will be excluded from the study.

The necessary information for obtaining inclusion and exclusion criteria will be extracted from hospital records, and if needed, the patient will be asked orally. The process of recruitment and randomization is illustrated in Fig. 1.

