### Interventions

Following the inclusion criteria, after explaining the objectives and method of the study, patients will be consciously entered into the study. They will be randomly allocated to either the intervention or control group. Patients in the NS oil group will receive two soft gels of NS oil, whereas the control group will receive two soft gels of paraffin oil (each soft gel weights 1 g). Treatment of both groups will last for 12 weeks. The selected dose is based on Kaatabi H [8], one of the best practical and safe interventions of NS oil supplementation in patients with diabetes mellitus. According to the predominant studies, NS oil supplementation in the mentioned dose and the term, but even in more prolonged use, did not have certain complications. Just in some rare cases, mild and temporary nausea and dyspepsia and decreased appetite have been reported [9, 10, 21]. The pharmaceutical company will prepare soft gels in a completely similar way in terms of shape, color, and odor. The preparation of black seed oil will be done by the cold press method by the pharmaceutical specialist.

The supplements will be available to attendees every two weeks. All patients will be asked about their usual dietary habits, physical activities, and drug regimens and report any possible changes. In addition, every 2 weeks, all patients will be evaluated by interview. Furthermore, the researcher will give participants a call number to inform him if there are any side effects or other problems Table 1.

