### Sample size

The sample size for this trial was calculated based on the primary outcome using the G-power software [23] (procedure of two independent groups) or formula $$ n=\frac{\left({\sigma}_1^2+{\sigma}_2^2\right){\left({Z}_{\frac{\alpha }{2}}+{Z}_{\beta}\right)}^2}{{\left({\mu}_1-{\mu}_2\right)}^2} $$. According to the previous results of NS on renal failure [1], the percentage reduction in creatinine (the primary outcome) is 32.43% in the NS group and 9.84% in the placebo group. By considering an alpha error of 0.05, and the power of 90%, the minimum sample size required for each group is 20 participants, in which with predicting a 15% loss, it will be 23 patients in each group. In total, 46 participants will be recruited in this trial.

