### Blinding

The study epidemiologist is responsible for randomization, and the study pharmacist is for blinding the supplements. The supplements, separated by letters A or B, are identical in shape, color, and odor and are placed in similar cans. So, participants, researchers, and data analysts will be blinded after determining interventions.

The blinding code will not be specified until the end of the study except in a medical emergency or a potential study-related adverse event determined by the principal investigator.

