### Ethics considerations

The expert nutritionist will explain the purpose of the study, benefits, or side effects to all patients before obtaining written informed consent. The volunteers will fill an informed consent form and enrolled in the study. They can withdraw their consent at any time study.

According to previous studies, this supplement’s use is safe in the dose, as mentioned earlier, and has no side effects. In case of any acute clinical symptoms due to supplementation, the subjects will be excluded, and the researcher will pay the costs of any possible complication. Any adverse events and other unintended effects of trial interventions will be collected and mentioned in the article.

The personal information of enrolled participants will be collected, shared, and confidentiality maintained before, during, and after the study by encoding systems. The results of the experiments will be available for participants at the end. The participants will be assured that the project will not be charged for treatment interventions. If NS supplementation is effective, the control group will also take this supplement.

The benefits of participating in this study for the control group are free:
Nutritional counseling and monthly monitoringGlycemic tests at the beginning and end of the studyKidney function tests at the beginning and end of the studyInflammation and oxidative stress status tests at the beginning and end of the studyBody composition and anthropometric tests at the beginning and end of the study

All results will be delivered to the participants at the end of the study.

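### Post-randomisation exclusions combined with deletion of missing data leave a comparison of non-excluded completers instead of the randomised groups; the size and direction of any bias are unknown

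*Protocol article*

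**What the plan says.** Three rules in the protocol article bear on who is analysed.

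- **Participants**, after the description of the common dialysis set-up: "In case of changes in hemodialysis method or type of dialysis filters, the person will be excluded from the study". A change of dialysis treatment is also listed among the exclusion criteria.
- **Ethics considerations**: "In case of any acute clinical symptoms due to supplementation, the subjects will be excluded".
- **Statistical analysis**: "Missing data will be removed from the final analysis".

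The surrounding design is as follows. "Treatment of both groups will last for 12 weeks" (Interventions), and Outcomes measures schedules blood at baseline and at the end of week 12 only. The between-group test is baseline-adjusted: "after the intervention, analysis of covariance (ANOVA) will be used by modulating the baseline values and probable variables". Sample size requires 20 per group and recruits 23 to allow for 15% loss. Blinding keeps the code closed "except in a medical emergency or a potential study-related adverse event determined by the principal investigator". The article names no analysis population, no follow-up of people who are excluded, and no sensitivity analysis that would offset the three rules.

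**The concern.** Randomisation makes the two groups comparable at allocation. That comparability carries to the analysis only if people are not removed for reasons that arise later and may be tied to arm or outcome. Both exclusions can arise later, and supplement-related symptoms cannot arise before the supplement is taken. With a single post-baseline measurement, a person who leaves in week 5 has no value to analyse, and the deletion rule then removes that person. Adjusting for the baseline value does not repair a selection that depends on what happened after baseline.

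What is at stake is whether a difference in creatinine, the other laboratory markers or the questionnaires at week 12 can be read as the effect of being assigned to NS. The abstract says there is no evidence that NS is safe in hemodialysis patients, so dropping symptomatic patients from the comparison also removes a group of particular interest.

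This is not a complaint that detail was left to an analysis plan. The article itself fixes both exclusions and the deletion rule, and a later plan could not recover week-12 values that were never collected.

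**Working it through.** **1. The plan's own loss figure.** Inputs from Sample size: 20 per group, 15% loss.

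- 20 × 1.15 = 23 per group, 46 in total, which is the stated figure. Dividing instead, 20 / 0.85 = 23.5, rounds up to 24; the difference is immaterial here.
- Expected number analysed: 23 × 0.85 = 19.55 per group, or 46 × 0.85 = 39.1 in total. So about 3 per group, 7 overall, are expected to be missing.

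**2. An SD for scale.** The article gives none, so this is an assumption. The planning effect is: "the percentage reduction in creatinine (the primary outcome) is 32.43% in the NS group and 9.84% in the placebo group". The difference is 32.43 − 9.84 = 22.59 points. Solving the article's formula for a common SD, with n = 20, two-sided alpha 0.05 and 90% power:

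SD = 22.59 / [√(2/20) × (1.960 + 1.282)] = 22.0 points.

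The answer is sensitive to this value: an SD of 18 would need 14 per group, and 25 would need 26.

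**3. What the allowance buys.** At SD 22.0, 20 analysed per group gives 90% power and 23 gives about 93.5%. Losses unrelated to arm and outcome would cost that much power and cause no bias. The allowance does nothing about losses that are related.

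**4. Bias with no true effect, by formula.** Assume 3 of 23 are removed from the NS arm only, and that they do g SD worse than those kept.

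- Shift = (3/23) × g SD.
- SE = √(1/20 + 1/23) = 0.306 SD.
- Type I error = 1 − Φ(1.96 − shift/SE) + Φ(−1.96 − shift/SE).

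| g | shift (SD) | shift (points, SD 22.0) | type I error |
|---|---|---|---|
| 0.5 | 0.07 | 1.4 | 5.5% |
| 1.0 | 0.13 | 2.9 | 7.1% |
| 1.5 | 0.20 | 4.3 | 9.8% |

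**5. Bias with no true effect, by simulation.** 23 per arm, SD about 22, 3 removed from each arm, two-sample t-test.

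| NS losses | control losses | bias towards NS (points) | type I error |
|---|---|---|---|
| from the worst half | from the worst half | about 0 | about 4.3% |
| from the worst half | random | about 2.7 | about 6.1% |
| the 3 worst outcomes | random | about 5.1 | about 13.8% |

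Against the planned 22.59 points, 2.7 is 12% and 5.1 is 23%. The last row is an extreme case: every NS loss must be exactly one of the three worst outcomes while control losses are unrelated to outcome. Swapping the arms reverses the sign of the bias. If both arms lose their three worst outcomes, the bias is again about 0, although the error rate is then 8.4% because trimming both tails makes the variance look too small.

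**The case against.** The strongest reply is that nothing in the document shows these rules favour NS. A reader might infer that dialysis is changed when clearance is poor, so that patients doing badly leave the NS arm. The article does not say why methods or filters change, and the rule applies to both blinded arms. With no true effect it would remove similar patients from each. If NS worked, more control patients might leave, which would bias against NS. A filter change may itself move creatinine and urea, so the exclusion may be a deliberate, if debatable, choice of what to estimate.

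A reader might also infer that symptom exclusions can occur only under NS. Under blinding, symptoms can equally be attributed to the paraffin capsules. The rule is limited to acute clinical symptoms, and Interventions describes the known effects as rare and mild. Nothing links them to a worse week-12 creatinine.

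The article also never says that data already collected from excluded people are discarded, and the symptom rule sits under Ethics considerations, where it reads as safety withdrawal.

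These replies stand against any claim about direction or a large expected bias. They do not remove the structural point. Blinding is incomplete for exactly the symptomatic patients, since the code may be broken for a possible study-related event. With no measurement between baseline and week 12, exclusion followed by deletion of missing data has the effect of a completers' comparison, whatever the intention.

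**Conclusion.** The point holds as a structural one. Followed as written, the rules in Participants, Ethics considerations and Statistical analysis compare non-excluded completers, not the groups that were randomised, and nothing in the article restores analysis as randomised.

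The direction and size of the bias are unknown. They depend on how many exclusions occur, in which arm and why. With no true effect, 3 of 23 lost per arm and an SD of about 22 points back-solved from the sample size formula, the bias runs from about zero (losses alike in both arms) through about 2.7 points with type I error about 6% (NS losses from the worst half, control losses random) to an extreme bound of about 5 points and about 14%. The stronger conclusions, that the plan is biased in favour of NS or that its error rate is near 14%, are not supported. Nor does the 15% allowance settle the matter, because it is a general loss figure for both arms, is not attributed to these exclusions, and protects power alone.

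**What to change.** - Reconcile the three sections so that stopping the supplement, or a change of dialysis method or filter, does not by itself end follow-up or inclusion in the analysis. The clinical rules for stopping the supplement are unchanged.
- Collect the week-12 outcomes (fasting blood, urine volume, questionnaires) from every randomised participant still reachable and consenting.
- Make the primary analysis one of all randomised participants in the arm assigned, with the baseline-adjusted model already planned.
- Report exclusions and losses by arm, with reasons.
- For outcomes still missing, add a delta or worst-case sensitivity analysis. Multiple imputation on arm, baseline and strata would not be enough: it assumes the data are missing at random given those variables, so it would not correct outcome-dependent loss, and it would be fragile with about 3 missing per arm across six strata.
- Keep the analysis without excluded patients as secondary.

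The cost is revised wording and a few extra week-12 assessments. Each needs a 12-hour fast, a urine collection and questionnaires, so it is more than a routine blood draw, although these patients attend two or three times a week. Including people who stopped or changed dialysis will dilute the effect somewhat. Trial status says the first-stage sampling is almost finished, so for anyone excluded who is already past week 12 only the reporting and sensitivity analysis remain possible.

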### Outcomes measures

Patients will be asked to obtain Informed consent. Next to that, everyone’s demographic and anthropometric indices checklist are filled, and a nutritionist will teach general nutritional recommendations. The dietary intake of individuals will be evaluated by the 3-day food registration questionnaire (two week days and one weekend day). Also, before the intervention, patients will be paid to complete their standard questionnaires, including KD-QOL and HADS, to assess the quality of life, depression, and anxiety. If the patient is illiterate, the information will be received by interviewing. At baseline and the end of the 12th week, 10 mL of blood will be obtained from each patient after 12 h of fasting. Blood serum will be stored at refrigerator temperature (− 70 °C).

The primary clinical outcome measures for the trial are renal function tests as creatinine, urea, uric acid, urine volume, indices related to blood glucose including FBS, HbA1c, GA, serum insulin, insulin resistance and β cell function, indices related to oxidative stress, and inflammation including SOD, MDA, TAC, and hs-CRP. Secondary outcomes include KDQOL and HADS questionnaires and the amount of energy and macronutrients intake.

The process for assessing the activity of hs-CRP, MDA, SOD, and TAC will be done by Navand assay kit (Navandsalamat, Iran) according to the company package insert instruction. The serum insulin level, HbA1c, and GA will be measured by the enzyme-linked immunosorbent assay (ELISA) method. Biochemistry Solutions will also measure creatinine, urea, uric acid, and FBS.

To determine insulin resistance and β cell function, HOMA-IR and HOMA-B formula will be used, respectively [22].

HOMA-IR=$$ \frac{\  glucose\left(\frac{mg}{dl}\right)\times insulin}{405} $$ HOMA-B =$$ \frac{fasting\ insulin\times 20}{fasting\ glucose-3.5} $$

The reliability of laboratory methods by sending the first ten samples of experiments with two different names to the laboratory expert and investigating the level of agreement between them will be determined. Also, body composition will be evaluated by the bioelectrical impedance analysis (BIA) method.

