### Stratified randomization

The patients will be allocated to either a NS oil or control group by block randomization after stratification based on the frequency of hemodialysis per week (2 or 3 times per week) and the amount of blood sugar (FBS < 120 mg/dL, FBS = 120–200 mg/dL and FBS > 200 mg/dL). This process will be carried out by a statistics specialist using RAS (random allocation software) in block sizes of 4.

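### The adjustment rule treats the two stratification factors as settled by matching and lists energy intake, a secondary outcome, as a covariate without limiting it to baseline

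*Protocol article*

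**What the plan says.** Four sections of the protocol article bear on this.

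- **Stratified randomization.** Allocation is in blocks of 4 after "stratification based on the frequency of hemodialysis per week" (two levels) and FBS (three classes: below 120, 120 to 200, above 200 mg/dL). This gives 2 × 3 = 6 strata.
- **Statistical analysis.** For normally distributed data, the comparison after the intervention is described as "analysis of covariance (ANOVA) will be used by modulating the baseline values and probable variables". Later: "The number of dialysis sessions per week and the participants’ blood sugar levels will be matched at the beginning of the study". The next sentence is the adjustment rule: "Other confounding factors such as energy intake, BMI, gender, and age will be adjusted if needed".
- **Outcomes measures.** "Secondary outcomes include KDQOL and HADS questionnaires and the amount of energy and macronutrients intake".
- **Interventions.** Among side effects that earlier studies saw only in rare cases, "mild and temporary nausea and dyspepsia and decreased appetite have been reported".

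**The concern.** Two things in the stated rule are badly fixed.

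First, the sentence on matching is followed directly by a sentence about other factors. Read together, they put the stratification factors aside because the design has balanced them, and reserve adjustment for different variables. Balance from stratified blocks does not replace having the factors in the model. The blocks make the arms more alike than simple randomisation would, but a model without the strata still counts the between-stratum variation as residual noise. The standard error is then too large for the design, and power is lost.

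Second, energy intake is named both as a confounder to adjust for and as an outcome of the trial. An outcome is measured after randomisation and may respond to treatment. If that measurement were the covariate, the treatment coefficient would no longer be the total effect of the supplement but the effect net of any change in intake.

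**Working it through.** **1. Are the strata in the model?** The ANCOVA sentence names the baseline values and an unspecified set of further variables. The matching sentence names dialysis sessions and blood sugar. The adjustment sentence names energy intake, BMI, gender and age. Dialysis frequency is never named as a covariate. FBS enters only as the baseline value when FBS is itself the outcome. The exclusion is implied, not stated outright.

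**2. What does omission cost with no baseline term?** Inputs from the protocol: N = 46, six strata, blocks of 4, two-sided 5% level. Assumed: equally likely strata, normal outcome with SD 1, and strata that explain a share R² of outcome variance. Simulated results for a linear model on arm alone, against arm plus strata:

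| R² | Type I error, no strata | Type I error, with strata | Power at 0.85 SD, no strata | Power at 0.85 SD, with strata |
|---|---|---|---|---|
| 0 | 5.1% | 5.2% | 80% | 80% |
| 0.1 | 4.0% | 5.0% | 82% | 85% |
| 0.3 | 2.2% | 5.2% | 83% | 91% |
| 0.5 | 0.9% | 5.2% | 86% | 98% |

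The error is on the conservative side throughout.

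**3. What does it cost with the planned baseline term?** The table above is not the analysis planned for normal data, because that analysis includes the outcome's baseline. The set-up was repeated with the baseline as covariate, assuming that the strata act equally on the baseline and week-12 values.

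- n = 40, within-stratum correlation 0.5 or 0.7, no strata in the model: type I error 4.4–4.8%, 4.1–4.6% and 4.3–4.5% at R² of 0.2, 0.4 and 0.6.
- n = 42, correlation 0.6: 4.0–4.5% without strata and 4.2–5.0% with them.
- The power difference under these assumptions is 0 to 5 points.

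Most of the loss in step 2 therefore disappears when the baseline carries the strata. When it carries them weakly, the loss is again large. The section on non-normal data is hard to follow but points to rank tests, which carry no baseline term.

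**4. Which energy intake is meant?** The Outcomes measures section describes the 3-day food record among the enrolment assessments, which suggests a baseline measurement. The same section makes energy intake a secondary outcome, which needs a later one. The adjustment rule does not say which is used. BMI has a milder form of the same ambiguity: the Ethics considerations section lists anthropometric tests at the beginning and end.

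**5. What would on-treatment adjustment do?** Let treatment shift intake by *a*, let the outcome depend on intake with slope *b*, and let the direct effect be *c*. The total effect is *c* + *a·b*; adjustment for intake returns *c*. With assumed *c* = 0.50:

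- *a* = *b* = 0.3: total 0.50 + 0.09 = 0.59; simulated adjusted estimate 0.50.
- *a* = *b* = 0.5: total 0.50 + 0.25 = 0.75; simulated adjusted estimate 0.50.

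This shows the mechanism only. The protocol gives neither *a* nor *b*.

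**6. Degrees of freedom.** Intercept, arm and baseline use 3, leaving 46 − 3 = 43, or 40 − 3 = 37 with the planned 20 completers per arm. The strata add 1 (frequency) + 2 (FBS class) = 3, leaving 40 or 34.

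**The case against.** The strongest reply is that the matching sentence merely describes stratified allocation, and that the open covariate wording could include the strata. That is possible, but such a reading leaves the point undecided, and the word that opens the adjustment sentence tells against it. The reply that the planned ANCOVA already recovers most of the precision is right whenever the baseline carries the strata. For FBS as outcome, the baseline value already carries the FBS factor. Energy intake stands beside BMI, gender and age, so a baseline value may well be intended; as a covariate it would be legitimate. The assessment timetable, which might settle this, is not visible.

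A reader might infer four stronger things that the protocol does not support.

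- **That the supplement lowers intake.** Decreased appetite is reported only in rare cases and among mild, temporary effects. That makes an effect on mean intake possible, not established. An example in which adjustment erases the whole effect has to assume that all of it runs through intake.
- **That the true type I error is far below 5%.** The low figures in step 2 belong to a test without the planned baseline term.
- **That baseline t-tests will decide which covariates enter.** The section does not link the two.
- **That the conditional wording by itself inflates type I error.** In simulation, taking the smallest p-value over all 16 subsets of four covariates raised it from 4.7% to 10.6%, but nothing in the plan describes such a search. A condensed article commonly leaves the exact covariate list to a fuller document.

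**Conclusion.** The point holds as a cheap improvement. The rule as written most naturally leaves dialysis frequency and FBS class out of the model and lets a trial outcome in as a covariate at an unstated time point.

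Omitting the strata does not bias the estimate. With the planned ANCOVA the cost is small where the outcome's baseline carries the strata: type I error about 4 to 4.5%, power lower by 0 to 5 points. It is larger where the baseline carries them weakly or is not in the model. These figures rest on assumed stratum effects and correlations; the protocol supplies none. The omission matters mainly for dialysis frequency and for the non-glycaemic outcomes.

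The concern about intake is conditional. It applies only if the post-randomisation value is used, and its size cannot be stated from the protocol.

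**What to change.** Replace the matching and adjustment sentences with a fixed model:

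- Regress the week-12 value on arm, the baseline value of that outcome, dialysis frequency (2 or 3 per week) and baseline FBS (the three classes, or continuous). When FBS is the outcome, its continuous baseline value can serve for both.
- Take any further covariates (age, gender, BMI, energy intake) at baseline only, and fix the list before unblinding.
- Do not adjust for post-randomisation intake in the primary analysis.

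The cost is wording plus about 3 degrees of freedom out of about 40. Sample size, visits and measurements do not change.
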